### Principles, theoretical basis and practical implementation of LC strategies

#### Understanding the patients’ perceived illness

##### Theory

The use of experienced patients is an innovative dimension in CR. This new approach requires health professionals to face the paradox between two aspects of sickness; ‘disease’ and ‘illness’, as introduced in 1978 by the American psychiatrist and anthropologist Kleinman. In this context, ‘disease’ refers to a malfunction of a biological process while the term ‘illness’ refers to the psychosocial experience and meaning of perceived disease [19]. The English sociologist Bury described chronic illness as a biographical disruption. He linked three aspects of disruption in development of a chronic disease; the disruption of taken-for-granted assumptions, the profound disruptions when the patient emerges from the illness and finally the disruption involving the patient’s mobilisation of resources to face his or her altered situation [20]. Charmaz took ‘biographical disruption’ a step further and called it a loss of self – a fundamental form of suffering in the chronically ill [21]. Disruption as described by Bury is a basic condition, and in order to search for meaning in life it is necessary to address the small routines of everyday life [20]. The individual’s account of the origin of their chronic illness in terms of causes can also, according to Williams, be read as an attempt to establish points of reference between body, self and society in reconstructing a sense of order from the fragmentation produced by chronic illness [22].

##### Practical implementation

When experienced patients tell their narratives about living with a heart condition, it is a way of integrating their perceptions about their illness with the professional’s knowledge about heart disease. The ‘illness’ term described by Kleinman is represented by the experienced patients while the ‘disease’ term is represented by health professionals. In this way, potential gaps in belief about disease between health professionals and patients can be bridged in the mutual ‘teaching room’. To support this, LC trained health professionals consistently focus on the participants’ everyday life during the group-based education and training sessions. They explore the patients’ daily routines as a means to help them bring order to their chaos and feelings of loss. Health professionals also address patients’ everyday lives in the individual clarifying interviews and allow patients to talk about the origin of their disease and their experiences of suddenly being ill.

#### Structured use of narratives

##### Theory

Narratives are described as a way of creating meaning, importance and consistency in the disorder, chaos and uncertainty that chronic illness brings [19, 22–25]. Telling a narrative about one’s illness has a potentially therapeutic effect especially on the narrator and also allows the audience to become involved in the story being told [26, 27]. Narratives are dynamic and in addition to creating order and structure out of past experiences, they give new perspectives to the present and assist in shaping the future. New experiences become meaningful when they are intertwined with existing experiences and existing experiences are reinterpreted and reshaped when they are entangled with new experiences [28]. Sharing brief examples of other, similar patients’ successes in changing a habit or solving a problem could be inspiring [29]. Narratives are not just mirrors of reality but are created in a relationship between the narrator and the audience. The listeners play an active role in the narratives and as such, expand reflections on possibilities for both health professionals and patients [26, 27].

##### Practical implementation

In the LC program, narratives from experienced patients are used as a method to bring experience-based knowledge about heart disease into teaching. These narratives aim to inspire patients to tell their own stories. Teaching is undertaken hand-in-hand with health professionals, who encourage participating patients to contribute their own narratives, providing new perspectives to the stories being told, creating a confident and trustworthy situation. The use of experienced patients and narratives in the LC program are steps in the process towards health behaviour change for participants. The power of having experienced patients who have changed a variety of behaviours during their lifetime assists the health professionals by showing them that participating patients are in fact able to make the necessary changes.

#### Understanding ‘learning’ as an ongoing process

##### Theory

The learning style in the LC program relies on the learning triangle developed by the Danish psychologist Illeris. He defines learning as an ongoing process consisting of two integrated processes of interaction and internalisation respectively, and describes learning as simultaneously comprising three different dimensions; cognitive, emotional and social. Learning and every single learning process reaches across these three dimensions. The ‘emotional drive’ for instance must be present for a learning process to become successful. If patients feel they are at risk, are uncertain, or have an unmet need, this impacts on their ability to learn. If the emotional or social dimension is not covered in a teaching situation the receiver attempts to restore the balance by developing greater sensitivity to themselves or their social environment [30].

##### Practical implementation

The health professionals in the LC program do not impose an ‘emotional drive’ on the patients, but instead try to motivate them to find the drive themselves in order to restore balance to the learning triangle. This helps the patients to understand learning as an ongoing process that they can integrate into the rest of their lives.

#### The appreciative approach

##### Theory

The overall approach in LC strategies is ‘appreciative inquiry’ as introduced by Cooperrider in 1987; a way of exploring patients’ previous experiences of using successful coping strategies earlier in their life. Applying strategies that have worked in the past to the future is a way of visualising the road to get there [31]. The ‘wanted’ future is connected to positive experiences in the past. Visions for the future, which the patients can identify with and which are created through talk, can create possibilities for behavior change instantly [32].

##### Practical implementation

To facilitate the appreciative approach the focus in the LC program is on the individual patient’s resources and successes, although their concerns are also valued. The aim of the initial clarifying interview is to initiate a developmental process in the patients before the rehabilitation program in order for them to achieve a better understanding of their needs, and with that knowledge prepare them for coping more easily in life. This awareness of the patient’s experiences and the building of a relationship provide valuable insights for the health professionals later in the group-based sessions where they can raise issues from the initial clarifying interview (if ethically acceptable). In the second interview at the end of the rehabilitation program, the health professional clarifies with the patient how they had benefited from the group-based sessions, and supports them to identify future strategies for coping with their chronic disease.

#### Motivating patients to change behaviour towards a healthier lifestyle

##### Theory

The individual interviews and the group based sessions are based on the concept of ‘motivational interviewing’ (MI) which has previously been shown to be effective in changing health behaviour, including in CR [33]. MI activates the patient’s own motivation to change health behaviour and adhere to a treatment plan. Motivation for change can be affected, worked with and developed in the context of a personal relationship. The concept relies on four main principles; roll with resistance, develop discrepancy, express empathy and support self-efficacy [29, 34].

##### Practical implementation

The purpose of having the experienced patients participate once a week in the training is to show that even experienced patients have varying exercise capabilities. Participating patients might thus identify with the experienced patients and be motivated to put extra effort into training.

#### Participant involvement by inductive teaching

##### Theory

Health professionals use four different types of questions throughout the LC rehabilitation program; lineal, circular, strategic and reflexive, in order to promote greater involvement from participants. The theoretical basis relies on the psychiatrist Tomm’s definition. He claims that the therapists must take responsibility for the questions they ask in order to increase the therapeutic value of the interview. The approach suggests that a particular question invites a particular answer, and that selecting either a lineal, circular, strategic or reflexive question restrains the range of “legitimate” responses and gives the health professionals influence in maintaining a direction for the conversation [35].

##### Practical implementation

This approach is demonstrated in the the LC training strategies, which aim to encourage participating patients to make exercise a part of their everyday life. The physiotherapist helps patients to identify challenges when exercising outside the hospital. They ask questions such as: Are you afraid when you feel your heart beat increasing? How do you cope with your body’s signals? How can you transfer this to your everyday life? Also the use of personal narratives about how patients manage the exercises at home and any challenges they experience is a central part of the training sessions, and is used to create reflections amongst patients. Health professionals request the patients to tell these stories either in the group-based setting or in a smaller personal context as a therapeutic attempt to bring order to their concerns and allay any anxiety about performing cardio stress exercises.

#### Homework for patients between sessions

##### Theory

Allowing time between the CR sessions is an important opportunity for the patients to achieve learning and coping skills that can eventually enhance their self-efficacy. The Danish and American anthropologists Grøn, Meinert and Mattingly define the concept ‘chronic homework’ as work that patients and families are expected to carry out in their home in order to manage their chronic condition. However, this chronic homework might look very different from the perspectives of health professionals and those of the patients. In their home, patients are unconsciously controlled by bodily habits and routines and it is thus important for health professionals to avoid the homework - as defined by the expert health sector - colonising the patient’s private sector. Therefore, the authors argue the need to look at chronic homework as a partnership that health professionals and patients must create with one another in a common understanding; a ‘borderland practice’ that moves between home and clinic, and is in continual need of reinvention as lives and home situations change [36].

##### Practical implementation

In the LC program, patients participate in defining their own homework between the CR sessions and health professionals help patients to integrate their acquired health-knowledge and concerns into their everyday lives.

#### Teaching the patients about stages of coping

##### Theory

Change is a process that involves progression through a series of different stages. This was defined in the theory ‘stages of change’ and contains the concepts: precontemplation, contemplation, preparation, action, maintenance and termination. Progress through the stages is not a linear process but consists of a spiral pattern whereby relapses to former stages can occur before reaching the maintenance or termination stage [37, 38]. For behaviour change to succeed and to build self-efficacy, people must feel threatened by their current behavioural patterns and believe that change of a specific kind will result in a valued outcome at an acceptable cost [39, 40]. Different ways of coping may influence behaviour change, and psychological and physical health outcomes [41].

##### Practical implementation

Different ways of coping are reviewed during the LC education sessions. An illustration of a spiral-formed coping circle is used in all group-based education sessions so patients can identify their stage of coping [42]. In that context, the health professionals emphasise to patients that healthy behaviour changes do not occur overnight but must be worked upon continuously.

### Evaluation meetings

The same team of nurse, physiotherapist and experienced patient conduct all the sessions during a period of eight week LC program. This reflective team evaluates the previous week in an hour-long meeting in which they discuss the overall sessions and needs of individual participants. The team evaluates what went well and what was less successful. They identify which experienced patient narratives worked as good learning examples in the ‘teaching room’ and discuss how health professionals can elaborate the narratives and make them generally applicable. In this scheduled evaluation, the team also makes plans for the following week’s education and training sessions.

### Summary of the intervention

Experience-based knowledge about heart diseases is integrated into LC CR via experienced patients as ‘bridge builders’ telling their narratives about how life can unfold when living with a chronic heart condition. Health professionals continuously address patients’ everyday lives in order to build partnerships in the ‘borderland’ between home and clinic. The educational tools rely on Illeris’ learning triangle and motivational interviewing whereby the health professional focuses on the theories of coping, ‘stages of change’ and ‘self-efficacy’. The LC strategies are tools to help health professionals understand how body, self and society interact and may contribute to building partnerships between patients and health professionals within their different contexts.

### Control group

Standard CR is characterised by a structured deductive teaching style with use of an identical pre-written slide show at all three hospital units. The eight week program is group based and the health professionals performing the training and education sessions are recruited from the cardiology wards and the departments of physiotherapy, respectively. They have not been given any formal education in CR but have achieved their skills by sitting in on sessions until they felt they were able to carry out the training and education themselves.

### Outcomes

The primary outcomes are adherence to CR, morbidity and mortality. Secondary outcomes are quality of life as well as lifestyle and risk factors. Socioeconomic variables and other relevant characteristics are collected at baseline.

Adherence to CR is assessed as completing the CR program, defined as having performed the second exercise bicycle test at the end of the program as well as determining the proportion of attended versus planned training and education sessions. Morbidity and mortality data will be drawn from the Danish National Patient Registry and the Danish CPR-registry. All readmissions after randomisation regardless of diagnosis will be included as the intervention is aiming more broadly than only heart disease-related events. Readmissions for IHD or HF as a sub-measure will also be assessed. Survival is measured as a combined endpoint of death, readmission with acute coronary syndrome, revascularisation or unstable angina. Data on medication compliance will be drawn from the Danish national medication profile as an independent variable.

Quality of life is measured with Short Form-12, version 2 (SF-12) questionnaire [43]. Furthermore, SF-6D is measured; this is a preference based measure of health derived from the SF-12 and often used as quality-adjusted life years (QALY) [44]. The Health education Impact questionnaire, version 3 is used to measure the patients’ coping ability. This is a questionnaire with high validity and reliability developed in Australia to evaluate the impact of patient education programs [45, 46]. Depression is assessed with the Major Depression Inventory. This questionnaire is validated in a Danish trial and has good accordance with depression diagnosis made by a psychiatrist [47].

Self-reported lifestyle and risk factors are measured with questionnaires on diet, smoking and exercise. Weight, height and waist circumference are measured by health professionals at all data collection times. Body composition of fat, muscle and bone are determined by DXA scans. Blood pressure is measured in a sitting position after 5 minutes of rest. Exercise work capacity is estimated from a maximum symptom-limited exercise test on a bicycle ergometer starting with 25 watts, adding 25 watts every 2 minutes. Lipid profiles include fasting triglycerides, total cholesterol, LDL-cholesterol and HDL-cholesterol.

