## Methods/Design

### Design

LC-REHAB was launched in three hospital units in Regional Hospital West Jutland (RHWJ), Denmark as an open randomised parallel group controlled study within which participants are allocated to either the intervention arm (LC strategies incorporated in standard CR) or to the control arm (standard CR). The randomisation is computer generated in a 1:1 ratio stratified for hospital unit, diagnosis (IHD or HF) and gender, alternating in blocks of two to four. According to power calculations, a total of 750 patients were needed to be recruited for the primary analysis. For secondary analysis of body compositions with Dual energy X-ray absorptiometry (DXA) scans, n = 150 patients were needed.

The CR program in both the intervention and control arms lasts for eight weeks, with training sessions three times a week and one education session per week. All sessions last 1.5 hours. In total, there are 24 training sessions and eight education sessions. The education in both arms is divided into eight topics; one topic per week. The topics are: function and symptoms of the heart, lifestyle effects on the development of IHD and HF, emotional reactions, medication, tiredness, the importance of relatives or other networks, importance and types of exercise, and future life with a chronic disease. The topics were elected on a theme day by LC educated health professionals and experienced patients with ‘The Disease Management Program for cardiovascular disease’ from Central Denmark Region as a general framework [18]. The training sessions are conducted by a physiotherapist in the presence of a nurse in case patients become unwell. The sessions consist of both cardio-stress and muscle-strengthening exercises. The education sessions are presented mainly by a nurse except for the topics on exercise and future life which are presented by the physiotherapist. In each arm of the study, patients are supported by the same team of nurse and physiotherapist throughout the eight week period.

Data is collected four times: at baseline, just after finishing the eight week CR program, three months after program completion, and at three years after program completion. A bicycle exercise test is conducted at all four data collection points (Figure 1).

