### Recruitment/settings

Study information is sent by mail to eligible patients and they are informed of the study via telephone by this paper’s first author. Informed consent is obtained one to two weeks after discharge by health professionals working in the CR units; either a nurse or a physiotherapist.

All CR programs start the first working day after randomisation and are performed in the CR units at each of the three hospitals. The majority of measurements are taken by health professionals or via questionnaires. Laboratory testing is performed at the hospitals’ laboratories, and DXA scans are performed at the Department of Nuclear Medicine within two of the three hospitals.

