### Statistical methods

Data is entered into dedicated databases and statistical analysis will be performed using STATA13 [49]. Cleaning and data management will be carried out on all relevant datasets and all statistical analysis will be performed using the ‘intention to treat’ principle. Descriptive statistics will be used to describe baseline variables. Differences in change in mean scores from baseline to follow-up between the two groups for continuous variables will be tested using unpaired t-tests provided they are normally distributed. Non-parametric tests will be performed for non-normally distributed data. Multiple regression analysis will be undertaken to check for interactions between gender, age and socio-economic background. For dichotomous variables, chi-square tests or logistic regression will be performed. Readmissions and survival will be analysed using Cox regression analysis.

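### Medication compliance, probably measured after randomisation, is made an explanatory variable with no window or model, and the interaction check as written leaves out treatment arm

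*Protocol article*

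**What the plan says.** **Medication compliance.** The Outcomes section names registry sources for morbidity and mortality, defines the readmission measures and the combined survival endpoint, and then adds: "Data on medication compliance will be drawn from the Danish national medication profile as an independent variable". No window, model or outcome is attached. Compliance is not named as a primary or secondary outcome. Baseline data are covered by a different sentence, "Socioeconomic variables and other relevant characteristics are collected at baseline", which does not name it either.

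**Timing of entry.** Under Recruitment/settings: "Informed consent is obtained one to two weeks after discharge by health professionals working in the CR units".

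**Link from arm to compliance.** The theory text on motivating patients, which describes the basis of the LC interviews and group sessions, says: "MI activates the patient’s own motivation to change health behaviour and adhere to a treatment plan".

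**Analysis.** Statistical methods commits every analysis to intention to treat. Changes in continuous outcomes "between the two groups for continuous variables will be tested using unpaired t-tests provided they are normally distributed". Dichotomous outcomes go to chi-square tests or logistic regression, and readmissions and survival to Cox regression. No covariates are listed for any of these, and compliance is not mentioned. The same section adds: "Multiple regression analysis will be undertaken to check for interactions between gender, age and socio-economic background".

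**The concern.** Randomisation protects the comparison of arms only while the model conditions on things fixed before allocation. In ordinary usage an independent variable is a regressor. The sentence assigning that role follows directly after the readmission and survival endpoints, which belong to the primary outcome domains and are to be analysed by Cox regression, where a regressor can be added. If compliance is measured during follow-up and LC improves it, adjusting for it removes the part of the LC effect that runs through better medication use. It also opens a path through any unmeasured factor that affects both compliance and prognosis. The result would be neither the effect of assignment nor a clean direct effect.

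The interaction sentence raises a different problem. Whether LC works differently in men and women, by age or by social background is a question about arm-by-factor terms. Interactions among the three factors answer a question about prognosis.

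**Working it through.** **1. Is compliance measured after randomisation?** The article does not say. Three facts point that way: it is listed with the follow-up registry data, it is not named with the baseline data, and consent comes one to two weeks after discharge, which leaves little time to observe compliance with discharge medication beforehand. This is an inference, though a good one.

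**2. Can the arm change it?** The motivational-interviewing text gives a pathway specific to LC. The medication education topic does not: the list in Design ("emotional reactions, medication, tiredness, the importance of relatives or other networks") applies to both arms.

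**3. What adjustment would do: linear illustration with assumed coefficients.** Let A be arm, M compliance, U an unmeasured common cause and Y the outcome:

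- M = a·A + u·U + error
- Y = 0.2·A + 0.3·M + u·U + error

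U and both errors have variance 1. The total effect of arm is 0.2 + 0.3a. After adjustment for M, the arm coefficient is 0.2 − a·u²/(1 + u²). With u = 0.5, u²/(1 + u²) = 0.25/1.25 = 0.2.

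| Shift in compliance by arm (a) | Total effect | Adjusted, u = 0 | Adjusted, u = 0.5 |
|---|---|---|---|
| 0 | 0.20 | 0.20 | 0.20 |
| 0.2 | 0.26 | 0.20 | 0.20 − 0.04 = 0.16 |
| 0.5 | 0.35 | 0.20 | 0.20 − 0.10 = 0.10 |

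A simulation of 2,000,000 subjects gave the same values to two decimals. The first row matters: if the arm does not move compliance, adjustment does no harm here. The direction in the last column depends on U acting with the same sign on M and Y, which is also assumed.

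**4. Hazard-ratio scale, assumed inputs.** Take a true readmission hazard ratio of 0.75 and a share p of the log effect running through compliance. Ignoring common causes, the adjusted ratio is approximately exp((1 − p)·ln 0.75):

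- p = 0.3: exp(0.7 × −0.2877) = 0.818
- p = 0.5: exp(0.5 × −0.2877) = 0.866

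The article states neither 0.75 nor a mediated share.

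**5. The interaction terms.** Write μ for the control mean and d for the LC effect in each gender-by-age cell (m/w for men/women, o/y for older/younger). With 1:1 allocation in each cell, the pooled cell mean is μ + d/2. The gender-by-age contrast is then

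(μ_mo − μ_my − μ_wo + μ_wy) + ½(d_mo − d_my − d_wo + d_wy).

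If LC works better in men by the same amount at every age, the d bracket is exactly zero and the contrast reflects prognosis only. Adding arm as a main effect does not help, because that fits one common LC effect. An arm-by-gender term is needed to see the difference.

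**6. Sample size.** With n per arm = 2(1.960 + 0.842)²·(sd/difference)²:

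- vitality: 2 × 7.849 × (24.4/5)² gives 374, or 748 in total
- mental health: 2 × 7.849 × (13.4/2.75)² gives 373, or 746 in total

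This reproduces the stated minimum of 750, with power 0.801 and 0.802 at 375 per arm. Nothing in this point alters it.

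**The case against.** The best defence is that the article does not put compliance into any stated treatment-effect model. Continuous outcomes are compared without adjustment, the Cox covariates are unlisted, and everything is under intention to treat. An independent variable could belong to a secondary explanatory analysis. All of that stands. A reader might infer that the LC effect will be biased and will lean towards no effect. The documents do not support that: it requires compliance to enter the effect model and LC to change compliance, and neither is stated. The size and direction also rest on inputs the article does not give.

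A reader might likewise infer that the interaction analysis is definitely mis-specified. The sentence follows the between-group comparisons and may be loose shorthand for interactions with arm, and the full model may sit in an analysis plan that is not shown. That is a fair reading, so the wording is ambiguous rather than proven wrong.

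Diagnosis is a stratification factor, but that does not oblige an interaction test with it. Making compliance a secondary outcome would add an endpoint the sponsor did not choose.

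The defence does not remove the point. An unseen plan can fill in what an article omits, but here the article assigns a role to one variable and names one set of interactions. Someone following either sentence literally could fit the wrong model.

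**Conclusion.** The point holds in conditional form. Compliance is given an explanatory role without a window or model, is probably measured after randomisation, and has a pathway from LC in the article's own theory. If it is entered in the readmission or survival models and LC affects it, the estimate departs from the intention-to-treat total effect. The size cannot be known from the article; under the assumed inputs, a hazard ratio of 0.75 would move to about 0.82 to 0.87, before any confounding between compliance and prognosis. If LC does not move compliance, or compliance stays out of the effect models, there is no bias of this kind.

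The interaction sentence as written cannot show whether the LC effect differs by gender, age or socio-economic background. The intended analysis may well be sound. Both sentences should be corrected before analysis; neither affects the planned sample size or power.

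**What to change.** 1. In Outcomes, replace the closing words on medication compliance with a statement of its measurement window and use. If it is measured after randomisation, say that it is kept out of the main treatment-effect models and used only descriptively by arm, or in an explanatory or mediation analysis labelled as such.
2. In Statistical methods, rewrite the interaction sentence as exploratory tests of arm by gender, arm by age and arm by socio-economic background, reported with confidence intervals. Arm by diagnosis is optional.

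The cost is two sentences. No new data are needed, and no endpoint or sample size changes.
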